**Objective:**

The CONFUSED study aims to identify molecular and clinical predictors of POD by integrating clinical data with proteomic, transcriptomic, and epigenetic analyses. The primary objective is to develop predictive models for POD using multimodal data. Secondary objectives include the identification of delirium-associated genes, proteins, and epigenetic signatures, as well as the exploration of patient subgroups at increased risk for POD.

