### Blood Sampling and Analysis

In addition, 20 mL of venous whole blood will be collected in ethylenediaminetetraacetic acid, serum, RNA exact, and DNA exact tubes (Sarstedt) at 4 points in time: during premedication, immediately postoperatively, on the second postoperative day, and on the fifth postoperative day. Serum and plasma samples, proteins, DNA, and RNA will be extracted from these whole blood samples. Furthermore, specific cell fractions such as neutrophils, macrophages, and peripheral blood mononuclear cells will be isolated. Proteins will be isolated from these cell samples and, together with plasma, subjected to the proteomic analysis using mass spectrometry to identify potentially significant proteins. Concurrently, an analysis of candidate genes, such as ACHE, BCHE, CHRNA7, chemokines, and cytokines, will be conducted to investigate methylation processes associated with the occurrence of POD. For methylation analysis, DNA samples are subjected to bisulfite conversion, and methylation will be quantified using quantitative polymerase chain reaction with specific primers [17]. The activity of acetylcholinesterase and butyrylcholinesterase will be assessed using ELISA (enzyme-linked immunosorbent assay).

In addition, an in silico analysis of the identified target genes will be performed to identify potential polymorphisms. Polymorphisms that appear potentially relevant will be genotyped in the entire patient cohort using the TaqMan Assay (TaqMan SNP Genotyping Assays; Thermo Fisher) [18,19]. In the final step, the identified genes and proteins will be quantified together with known inflammatory markers (tumor necrosis factor-α, interleukin-6 [IL-6], and interleukin-10) from serum samples using ELISA or the LegendPlex assay (BioLegend) [20]. The blood plasma obtained during cell isolation will also be used for measuring tumor necrosis factor-α and other cytokines (IL-6, interleukin-10, etc) via ELISA. In addition, neuron-specific enolase and S-100 β protein levels will be determined from the remaining blood preoperatively and 48 hours and 5 days postoperatively. The remaining DNA, RNA, and plasma samples will be stored at −20 °C and −80 °C to ensure the possibility of repeat measurements in case of technical errors. The samples will also be preserved for further validation of significant proteins from the proteomic analysis using ELISA and to investigate their genetic basis (polymorphisms and DNA methylation).

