### Clinical Data Collection and Processing

A formal Data Monitoring Committee is not required for this study, as there are no interventions being tested and no anticipated risks to participants beyond standard clinical care. Therefore, no interim analyses or stopping guidelines are planned.

The study conduct will be monitored by the study physician and the research team according to standard operating procedures to ensure data quality and protocol adherence. Since there are no safety concerns beyond routine care, no additional independent monitoring is planned.

Clinical parameters are systematically documented and collected throughout the project. These parameters are exported from the routine medical documentation within the various subsystems of the electronic health records. On regular wards, this will be done through the Hospital Information System, and in ICUs, through the Patient Data Management System, capturing the entire course of patient treatment. The clinical data include vital parameters, medications, diagnoses, procedures, and laboratory values. Anesthesia documentation is supplemented by a digital Anesthesia Information Management System, which closely monitors all perioperative anesthesia parameters, including medication, vital signs, and ventilation parameters. Intraoperative electroencephalogram data, recorded during anesthesia depth monitoring, will also be captured.

These routinely collected data will be supplemented by explicitly requested variables to determine study end points, such as delirium scores. For this purpose, a study nurse will assess delirium preoperatively, upon transfer from the recovery room, and on the 5 subsequent postoperative days using the CAM, or CAM-ICU if the patient is transferred to the ICU. A learning effect from repeated testing is only to be expected in patients without delirium. Other outcome parameters include neuropsychological status measured by the Repeatable Battery for the Assessment of Neuropsychological Status, health-related quality of life assessed with the 36-item Short Form Health Survey, and mortality on the day of hospital discharge, as well as on days 30 and 90 after surgery.

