The OMOP CDM standard includes the representation of clinical content using standardized vocabularies, enabling the mapping of primary data from various data standards (eg, International Classification of Diseases, 10th Revision [ICD-10] and German Procedure Classification System [OPS]) and facilitating conversion to modern data ontologies such as SNOMED-CT (Systematized Nomenclature of Medicine—Clinical Terminology) and/or LOINC (Logical Observation Identifiers Names and Codes). Furthermore, OMOP CDM supports the eventual integration into the developing research data infrastructure of the Medical Faculty at Ruhr University Bochum, potentially using Health Level Seven Fast Healthcare Interoperability Resources (HL7 FHIR) profiles. This infrastructure constitutes the integration pathway for clinical deployment. Clinical input data (eg, demographics, vital signs, laboratory values, medications, and delirium assessments) are captured automatically from the Hospital Information System, Patient Data Management System, and Anesthesia Information Management System without additional manual data entry by clinical staff, and risk predictions are generated automatically within existing workflows at the point of care. For the preoperative clinical model, all input variables are documented as part of standard preanesthesia assessment, and no laboratory analyses are required, meaning a risk prediction is available immediately at the time of the outpatient consultation with no analytical turnaround time. For the integrative postoperative model, predictions are updated automatically as new data are entered into the electronic record, ensuring timely availability for clinical decision-making throughout the hospital stay.

The processed clinical data will then be combined with data from subsequent work packages to support the development of an artificial intelligence (AI) model. Individual deidentified participant data (including the data dictionary), statistical code, and any other materials will be accessible to authorized personnel of the AI Center.

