### Integrative Data Analysis and AI Model Development

This section describes the planned integration and analysis of clinical and multiomics data for the exploratory investigation of potential predictors of POD. Data will be analyzed both independently and in combination with a focus on patient groups with and without POD. Prior to analysis, clinical datasets will be preprocessed; for example, variables with more than 30% missingness will be discarded, whereas remaining gaps will be imputed, where applicable, when missing at random, using multiple imputation by chained equations or other suitable methods. Clinical continuous variables will be centered and scaled to *z* scores, and categorical variables will be one-hot encoded. In proteomics, the analysis will involve deriving accurate quantitative protein data from peptide data, particularly by improving the utilization of shared peptides found in multiple proteins.

Univariate analyses, such as *t* tests and ANOVA (with adjustments for multiple comparisons), will be applied to identify candidate features, which may subsequently be subjected to pathway and enrichment analyses to generate mechanistic hypotheses regarding molecular processes potentially involved in POD. Multivariate techniques, including principal component analysis and clustering, will be applied to uncover latent patient phenotypes beyond a priori groupings.

The significant findings from clinical and omics data are fed into a knowledge base for targeted searches, facilitating focused investigations (targeted proteomics). The entire dataset is also analyzed using multivariate methods, including principal component analysis and clustering, to reveal latent patient phenotypes beyond a priori groupings. Supervised prediction of POD will rely on a benchmark suite of algorithms (eg, regularized logistic regression, random forests, support vector machines, and gradient-boosting methods). Model training and hyperparameter tuning will follow a nested cross-validation scheme, supplemented by a temporally separated holdout set when sufficient data are available. Discrimination and calibration will be reported with area under the receiver operating characteristic curve, area under the precision-recall curve, sensitivity, specificity, accuracy, and *F*-score. The final modeling protocol will be chosen on the basis of performance, interpretability, and clinical plausibility and can be iteratively updated as additional data accumulate.

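### Clustering is set on the entire dataset with no time limit, so clusters read as subgroups at increased risk for POD may partly reflect POD or its consequences

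*Protocol article*

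**What the plan says.** The Abstract (Objective) lists among the secondary objectives "the exploration of patient subgroups at increased risk for POD". In Integrative Data Analysis and AI Model Development, PCA and clustering are named twice; the second time the input is stated: "The entire dataset is also analyzed using multivariate methods, including principal component analysis and clustering, to reveal latent patient phenotypes". Neither mention gives a time limit or excludes outcome variables.

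Other Methods sections show what has been collected:

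- **Clinical records.** Clinical Data Collection and Processing describes ward and ICU records "capturing the entire course of patient treatment. The clinical data include vital parameters, medications, diagnoses, procedures, and laboratory values".
- **Delirium scores.** The same section says: "These routinely collected data will be supplemented by explicitly requested variables to determine study end points, such as delirium scores".
- **Blood samples.** Blood Sampling and Analysis sets the draws "during premedication, immediately postoperatively, on the second postoperative day, and on the fifth postoperative day". Table 1 marks the last draw under day 4 rather than day 5. Either day lies within the five postoperative days on which delirium is assessed.

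The same analysis section does restrict one model, the preoperative clinical model, to variables known at the preanesthesia clinic. It states no such restriction for the clustering.

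**The concern.** Being at increased risk is a statement about the time before the event. A group shows prior risk only if it is formed from information that precedes POD. For a patient who becomes delirious on day 1, the day 2 proteins, later medications, new diagnoses and any ICU data can all be consequences of the delirium. If such variables help to form the clusters, patients are partly sorted by whether they had POD, and a comparison of POD incidence between clusters is then partly circular.

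A high-risk phenotype could then appear even if nothing measured before surgery carried information about POD. It could not be recognised before surgery, and it could misdirect the later validation work that the article foresees. It would also work against the article's own wish for phenotypes that go beyond the groupings already known, because clusters driven by consequences of POD tend to return the split between patients with and without it.

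**Working it through.** The article gives no figure to reproduce here. The check has two parts.

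**1. Which variables follow POD onset?** POD is assessed in the recovery room and on postoperative days 1 to 5. Table 1 then gives:

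- Proteomics, ELISA and cell isolation continue on day 2 and at the last draw. Acetylcholinesterase is measured daily to day 5. These can follow onset.
- Clinical parameters and progress documentation run to discharge. These can follow onset.
- RNA microarray and epigenetic analysis are marked only at baseline and in the recovery room, and genotyping only at baseline. These layers have no day 2 or later sample.

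So the concern applies to the clinical, protein and enzyme data, not to every omics layer.

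**2. How large could the effect be?** From the article: 24% incidence, and 300 patients (the upper end of its range), so 0.24 × 300 = 72 expected cases. Everything else is an assumption: z-scored data, k-means, baseline variables unrelated to POD, and *p* post-onset variables shifted by *d* SD in cases. The POD rate of a cluster is its cases divided by its patients.

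The pull of POD on the clustering is roughly the squared distance between the case and non-case means, *p* × *d*²:

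- 10 variables at 0.5 SD: 10 × 0.25 = 2.5
- 20 variables at 0.5 SD: 20 × 0.25 = 5.0
- 10 variables at 0.8 SD: 10 × 0.64 = 6.4

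Mean POD rates with 30 unstructured baseline variables and three clusters:

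| Variables clustered | Highest | Lowest | Runs with chi-square p < 0.05 |
|---|---|---|---|
| Baseline only | 28% | 20-21% | 6-7% |
| + 10 at 0.5 SD | 37% | 13% | 84% |
| + 20 at 0.5 SD | 55% | 6% | 100% |
| + 10 at 0.8 SD | 64% | 4% | not tabulated |

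With 10 variables at 0.3 SD, 34% of runs were significant. A second design (20 baseline variables, two clusters) agrees: 26% against 22% for baseline only, 34% against 14% at 0.5 SD, and 57% against 3% at 0.8 SD. None of these runs used delirium scores. Adding five daily delirium results instead (assumed positive on 60% of days in cases) gave 100% against 3%.

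The effect shrinks when the baseline data have structure of their own. Take three real baseline groups whose means vary by 0.5 SD on each of 30 variables. The expected squared distance between two group means is 30 × 2 × 0.25 = 15, well above 2.5. With three clusters these groups take up all the clusters, and 10 variables at 0.5 SD give only 27-28% against 19-20%, with 8-10% of runs significant. With four clusters one is free again: 34% against 15%, with 37% significant. With 500 unstructured baseline variables, 10 shifted variables give 29% against 19%, and 100 shifted variables (100 × 0.25 = 25) give 68% against 5%.

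**The case against.** The strongest reply is that the article never says the clusters are the risk subgroups, nor that POD incidence will be compared across them. Their stated purpose is latent phenotypes, for which full-course data are legitimate. Univariate comparisons and the supervised models with feature attribution can also describe who is at higher risk. The feature list may stand in the analysis plan, which is not shown. Prevention is assigned to the preoperative clinical model, and the whole study is labelled exploratory.

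Much of this stands. The link to the secondary objective is an inference, drawn because no other unsupervised subgroup method is described. The harm does not reach the preoperative clinical model. It does not remove the point, however. The article states the clustering input, and states it without a time limit. An exploratory label allows for uncertain findings but does not cure groups formed partly by the outcome.

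A reader might go further and infer that delirium scores are clustering features, so that the risk groups will be defined by POD itself. The documents do not support this. In context, the entire dataset is set against the significant findings of the sentence before, and may mean all features rather than pre-selected ones. Delirium scores are introduced as end-point variables. The sentence "Clinical input data (eg, demographics, vital signs, laboratory values, medications, and delirium assessments) are captured automatically" describes the data path for deployment, not the clustering. The concern does not need the scores: later samples and later care are enough.

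**Conclusion.** The point holds as a risk, not as a certainty. If the clustering is carried out as written and its clusters are reported as subgroups at increased risk for POD, they may partly reflect POD or its consequences. The distortion ranges from about chance (27-28% against 19-20%) to very large (64% against 4%, or 68% against 5% with many shifted variables). No single figure should be quoted as the expected size, because the article fixes neither the number of clusters nor the feature set, and baseline structure and post-onset shifts are unknown. The conclusion rests on reading the entire dataset as including postoperative data, which the text supports, and on the clusters serving the subgroup objective, which is inferred. The weight is minor to moderate because the analysis is exploratory and the supervised preoperative model is unaffected.

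**What to change.** Add one sentence to Integrative Data Analysis and AI Model Development: clusters reported as subgroups at increased risk for POD are formed only from data available before surgery (baseline clinical variables and the preoperative blood sample), delirium scores are excluded, and POD incidence is then compared across the clusters. Clustering on the full course may stay, labelled as a description of the postoperative course and not as risk subgroups. A bootstrap check of cluster stability would be a useful addition.

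The cost is one extra clustering run and fewer variables in the risk phenotypes. Recruitment is ongoing and the final data lock is still ahead, so the change can still be made.

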Given the limited sample size relative to the high-dimensional omics data, all predictive models are exploratory and hypothesis-generating. External validation in independent cohorts will be necessary to confirm predictive performance and clinical utility. Models trained on clinical variables alone will be benchmarked alongside multiomics models for exploratory comparison, reflecting potential applicability in settings where omics data are not routinely available.

The final operating threshold will be selected to prioritize either sensitivity (screening scenario) or specificity (confirmatory setting), as dictated by the clinical use case. Alongside the integrative models, versions limited to routinely available clinical variables will be trained and benchmarked to ensure bedside applicability where omics data are not regularly available. To interpret the resulting models, feature-attribution techniques such as SHAP (Shapley Additive Explanations) values will quantify and visualize each variable’s influence on the prediction, thereby generating mechanistic hypotheses about the molecular and functional pathways leading to POD. To clarify the clinical deployment strategy, the study is designed to yield 2 distinct and complementary model types. The first is a purely preoperative clinical model, trained exclusively on variables available at the preanesthesia outpatient clinic, specifically the DRAS, Mini-Mental State Examination score, age, comorbidities, surgical type, and medication profile. This model requires no blood sampling and can generate a risk prediction at the time of the outpatient consultation, typically days to weeks before surgery. This is the primary bedside instrument of the study and the relevant window for initiating preventive measures, including medication review and reduction of anticholinergic burden, sleep hygiene counseling, optimization of sensory aids, cognitive stimulation, and planning of early postoperative mobilization. The second is an integrative multimodal model incorporating longitudinal biomarker data from all 4 perioperative collection time points. This model serves a distinct purpose: continuous refinement of risk estimates throughout the hospital stay, enabling early detection of evolving POD in the postoperative period. Postoperative biomarker data are therefore not a prerequisite for preoperative risk stratification but an additional layer extending clinical utility into the postoperative setting.

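### The plan promises to report calibration, but none of the six performance measures it names for the purpose measures calibration

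*Protocol article*

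**What the plan says.** All places are in the Protocol article.

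- **Integrative Data Analysis and AI Model Development**, performance sentence: "Discrimination and calibration will be reported with area under the receiver operating characteristic curve, area under the precision-recall curve, sensitivity, specificity, accuracy", and F-score. The list is not marked as a set of examples, whereas the list of algorithms shortly before it is ("regularized logistic regression, random forests, support vector machines, and gradient-boosting methods"). Calibration is mentioned nowhere else in the article.
- **Same section**, on the cut-off: "The final operating threshold will be selected to prioritize either sensitivity (screening scenario) or specificity (confirmatory setting), as dictated by the clinical use case".
- **Same section**, on the preoperative clinical model: it "can generate a risk prediction at the time of the outpatient consultation, typically days to weeks before surgery", and "This is the primary bedside instrument of the study and the relevant window for initiating preventive measures". The integrative model is meant for "continuous refinement of risk estimates throughout the hospital stay, enabling early detection of evolving POD in the postoperative period".
- **Clinical Data Collection and Processing**, on deployment: "risk predictions are generated automatically within existing workflows at the point of care".
- The final model is to be chosen on performance, interpretability and clinical plausibility. Performance is not defined further.

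**The concern.** The sentence gives one list of measures two jobs, and the list can do only one of them. Discrimination asks whether patients who develop delirium are ranked above those who do not. Calibration asks whether, among patients given a risk of 40%, about 40% develop delirium. A model can do well on the first and badly on the second.

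This matters here because the output is described as a risk prediction at the outpatient visit and as risk estimates refined during the stay, not only as a yes/no flag. A clinician who reads a stated risk relies on its size. The algorithms compared also differ in how directly they yield probabilities; support vector machine scores are not natively probabilities. If the sentence is followed literally, the study reports no evidence on whether the stated risks are right.

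**Working it through.** The article gives no calibration figure, so there is nothing to reproduce. The check is whether each named measure responds to miscalibration.

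**Step 1: what each measure depends on.**
- AUROC and AUPRC are functions of the ranks of the predictions. Any strictly increasing distortion of the risks leaves them unchanged, without condition.
- Sensitivity, specificity, accuracy and F-score are functions of the 2x2 table at a cut-off. A strictly increasing distortion leaves them unchanged if the cut-off moves with it. At a cut-off fixed on the probability scale they may or may not change.

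**Step 2: simulation.** Inputs: incidence 24% (Sample Size Considerations). Assumed: normally distributed log-odds with SD 1.1, which gives an AUROC of about 0.76; cut-off set for about 80% sensitivity; n = 200,000. The true-risk model is compared with two distorted versions: log-odds multiplied by 2.5, and log-odds plus 1.5.

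| | True risks | Log-odds x 2.5 | Log-odds + 1.5 |
|---|---|---|---|
| AUROC | 0.7605 | 0.7605 | 0.7605 |
| AUPRC | 0.5116 | 0.5116 | 0.5116 |
| Sensitivity, cut-off moves | 0.800 | 0.800 | 0.800 |
| Specificity, cut-off moves | 0.567 | 0.567 | 0.567 |
| Accuracy, cut-off moves | 0.623 | 0.623 | 0.623 |
| F-score, cut-off moves | 0.504 | 0.504 | 0.504 |
| Mean predicted risk (observed 24.0%) | 24.0% | 13.9% | 51.6% |
| Calibration slope | 1.00 | 0.40 | 1.00 |
| Brier score | 0.152 | 0.170 | 0.235 |

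The six named measures do not separate the three models. Mean predicted against observed risk, together with the slope, does. The measures also agreed across models at n = 300 and n = 417.

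**Step 3: the same models at a fixed cut-off of 0.5.**

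| | True risks | Log-odds x 2.5 | Log-odds + 1.5 |
|---|---|---|---|
| Sensitivity | 0.252 | 0.252 | 0.807 |
| Specificity | 0.951 | 0.951 | 0.557 |
| Accuracy | 0.783 | 0.783 | 0.617 |
| F-score | 0.358 | 0.358 | 0.503 |

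Multiplying the log-odds by 2.5 changes nothing, because a predicted risk of 0.5 has log-odds zero and stays there. The shift does change the four measures, but not in a way that can be read as calibration: sensitivity and F-score rise while the Brier score worsens from 0.152 to 0.235.

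**Step 4: what miscalibration could mean for one patient (illustration only).** Suppose the predicted log-odds are too extreme around the 24% base rate:

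logit(predicted) = b + m x (logit(true) - b), with b = ln(0.24/0.76) = -1.153 and calibration slope 1/m.

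Example with m = 2 (slope 0.5) and true risk 40%: -1.153 + 2 x (-0.405 + 1.153) = 0.342, which is a predicted risk of 58%.

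| True risk | Slope 1.0 | Slope 0.5 | Slope 0.4 |
|---|---|---|---|
| 10% | 10% | 4% | 2% |
| 40% | 40% | 58% | 67% |
| 60% | 60% | 88% | 94% |

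The slopes are assumptions. The documents give no basis for predicting which would occur. In this example the 40% patient crosses 0.5, so the four cut-off measures could change at that fixed cut-off. AUROC and AUPRC could not.

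**The case against.** - **The commitment to calibration is there, and the SAP may supply the measures.** Trial Status says a statistical analysis plan exists, and the article says it follows TRIPOD. This stands as a limit on the consequence, but it does not cure the sentence: the article does not leave the measures open, it names them, and they are the wrong ones.
- **The models are exploratory.** Sample Size Considerations and the modelling section say so, and the Introduction plans validation in a new independent cohort. This stands and lowers the severity.
- **All six measures are blind to miscalibration.** A reader might infer this on the view that the cut-off is taken from the data. The article says only that the clinical use case dictates it. Only AUROC and AUPRC are blind without condition; Step 3 shows that the other four can move at a fixed cut-off.
- **A miscalibrated tool would pass unnoticed, and model choice ignores calibration.** A reader might infer both. The documents support neither: external validation could reveal the fault, and performance is not defined as these six measures alone.
- **The patient-level figures estimate this study's error.** They do not. The overfitting the article warns of concerns high-dimensional omics data, while the preoperative model uses clinical variables only, and regularization and nested cross-validation are planned.
- **Accuracy should be dropped because it misleads when delirium is the minority outcome.** This is a preference, not an error. A rule that labels nobody has zero sensitivity, which is in the same list.

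**Conclusion.** The sentence is wrong as written. It says calibration will be reported with six measures, and none of them measures it; that follows from their definitions and needs no assumption. The simulation shows how large an undetected discrepancy can be: mean predicted risk from 13.9% to 51.6% against 24.0% observed, with the six measures identical. It rests on the article's 24% incidence, an assumed spread of risk, two chosen distortions and a cut-off that moves with the predictions. It does not forecast how badly the study's models will be calibrated.

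The severity is should-fix. The article describes bedside risk predictions, so calibration is relevant. But the models are exploratory, external validation is planned, and calibration can still be computed from stored predictions.

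**What to change.** Amend the performance sentence so that each property has its own measures:

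- **Discrimination:** AUROC and AUPRC.
- **Classification at the chosen threshold:** sensitivity, specificity, accuracy and F-score.
- **Calibration:** calibration intercept, calibration slope and a calibration plot. Add the Brier score as an overall measure; it mixes discrimination and calibration, so it should not stand in for the other three.

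Compute the calibration measures from the outer-fold predictions of the nested cross-validation and from the holdout set if there is one. State that performance, as used in choosing the final model, includes calibration. If the SAP already names such measures, align the two texts.

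The cost is one reworded passage and a few lines of analysis code, with no new data. Recruitment is ongoing and final data lock has not occurred, so the change can still be made in time.

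### The final algorithm is chosen partly on observed performance, and nothing places that choice inside the nested cross-validation, so the reported internal AUROC is likely to be optimistic

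*Protocol article*

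**What the plan says.** All of this is in the protocol article, Integrative Data Analysis and AI Model Development.

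- **Candidates.** Supervised prediction uses a "benchmark suite of algorithms (eg, regularized logistic regression, random forests, support vector machines, and gradient-boosting methods"). The list is open and names four families.
- **Scope of the resampling.** "Model training and hyperparameter tuning will follow a nested cross-validation scheme, supplemented by a temporally separated holdout set when sufficient data are available". Choosing between algorithms is not among the tasks named. The holdout is conditional and is not said to be kept out of that choice.
- **Selection rule.** "The final modeling protocol will be chosen on the basis of performance, interpretability, and clinical plausibility", and this protocol "can be iteratively updated as additional data accumulate".
- **Metrics.** Six are listed: "area under the receiver operating characteristic curve, area under the precision-recall curve, sensitivity, specificity, accuracy, and *F*-score". None is named as the one that decides, and no minimum level is set.
- **Threshold.** "The final operating threshold will be selected to prioritize either sensitivity (screening scenario) or specificity (confirmatory setting), as dictated by the clinical use case".
- **Outputs.** Two model types are fixed in advance: a preoperative clinical model and an integrative multimodal model. All models are called exploratory, and external validation in independent cohorts is said to be necessary.

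Sample Size Considerations and Comparison With Existing POD Prediction Models both cite nested cross-validation as a safeguard. Neither says that it covers the choice of algorithm.

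**The concern.** The outer loop gives a fair estimate of performance for any procedure that is fixed before the outer test folds are seen. That holds for each algorithm taken alone. It does not hold for the algorithm picked because its outer-fold result was the highest, since the pick favours the candidate that chance has helped.

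The article gives nested cross-validation one scope and then states a performance-based choice that this scope does not include. On the natural reading, the same outer-fold results choose the winner and are published as its performance. With no minimum level, a final model is named whatever the data show.

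At stake is the main internal result for each of the two models. One of these is described as the study's primary bedside instrument, and the models are also to be interpreted through feature attribution.

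**Working it through.** **Plan figures.** The article gives no AUROC target, so there is none to reproduce. Its usable inputs, from Sample Size Considerations, are 100 POD cases and a total of 200 to 300 patients, which leaves 100 to 200 controls. The main case below uses 200. At the article's own 24% incidence, 100 cases would need 100/0.24 = 417 patients, or 317 controls. That mismatch is a separate matter and serves here only as a sensitivity case.

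**Assumptions.** Four candidates per model type; correlation rho between candidate AUROCs of 0 to 0.8; the winner is the candidate with the highest AUROC.

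**Step 1. Precision of one AUROC with no signal.** SE = sqrt((n1 + n0 + 1)/(12 n1 n0)) = sqrt(301/240,000) = 0.0354.

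**Step 2. Best of four, normal approximation.** The expected maximum of four independent standard normals is 1.029, so the mean of the winner is 0.5 + 1.029 × SE × sqrt(1 − rho).

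| rho | Mean of winner | Lower 95% limit above 0.5 |
|---|---|---|
| 0 | 0.536 | 9.6% (1 − 0.975^4) |
| 0.5 | 0.526 | 7.9% |
| 0.8 | 0.516 | 5.6% |

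The percentages for rho of 0.5 and 0.8 come from 100,000 draws. A single candidate gives 2.5%.

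**Step 3. Simulation with refitting.** Pure-noise data in four sets of 15, 200, 300 and 30 variables plus their union; four simple learners standing in for the named families; 5-fold cross-validation. The limit is crossed when AUROC > 0.5 + 1.96 × SE. Each cell gives the mean AUROC and the share of runs crossing the limit.

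| Controls (runs) | Best of four, combined data | One prespecified model | Choice made in the inner loop |
|---|---|---|---|
| 100 (200) | 0.532; 19.5% | 0.499; 7.5% | 0.495; 7.0% |
| 200 (200) | 0.535; 20.5% | 0.501; 5.5% | 0.502; 5.0% |
| 317 (100) | 0.527; 20.0% | 0.505; 7.0% | 0.498; 5.0% |

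Four cautions:
- The Monte Carlo SE of 20.5% is sqrt(0.205 × 0.795/200) = 2.9 percentage points.
- The prespecified model used the 15-variable set and the best-of-four contest used the combined set, so the two columns are not exactly matched.
- Even the prespecified model exceeds 2.5%, so part of the excess over nominal comes from the limit used and not from selection.
- The inner-loop column chose among all 20 combinations of learner and data set, a harder test than four, and still returned about 0.50.

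**Step 4. A real signal, true AUROC 0.70 for all four.** Hanley-McNeil variance with A = 0.70: Q1 = A/(2 − A) = 0.5385, Q2 = 2A²/(1 + A) = 0.5765, A² = 0.49.

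Variance = [0.70 × 0.30 + 99 × 0.0485 + 199 × 0.0865]/20,000 = 22.2/20,000 = 0.00111, so SE = 0.0333.

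Mean of winner = 0.70 + 1.029 × 0.0333 × sqrt(1 − rho) = 0.734 at rho = 0 and 0.715 at rho = 0.8. The optimism is about 0.015 to 0.034.

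**The case against.** The best defence is that the article does not say where algorithms are compared. Trial Status says that a full protocol and an analysis plan exist, and these may put the choice in the inner loop. That stands as far as it goes: placing the choice outside the loop is an inference. But the article does more than stay silent. It states a scope for the resampling and a selection rule, and the second is not covered by the first.

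The rule also weighs interpretability and plausibility, so the top-scoring algorithm need not win. The figures above are therefore an upper bound for a given number and correlation of candidates. Nor does the article say that only the winner will be shown.

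The holdout, the exploratory label and the required external validation are genuine protections against over-use of the model. They do not alter the internal AUROC that is published, and the holdout helps only if it exists and plays no part in the choice.

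A reader might infer several stronger claims that the document does not support:
- **One contest across all data layers.** The sentence "Data will be analyzed both independently and in combination with a focus on patient groups with and without POD" introduces the analyses and is not a rule for picking one winner. Two model types with different purposes are fixed, and clinical-only and multiomics models are compared for exploration only. Results for 8 or 20 competing candidates therefore do not describe this plan.
- **A convincing model always emerges from noise.** Some model is always named, but with four candidates the lower limit would still not exceed 0.5 in about 79% to 94% of null studies.
- **A published confidence interval that ignores selection.** The article specifies no interval; the limit used above is only a yardstick.
- **Feature attributions presented as established pathways.** They are offered as a source of hypotheses.
- **The threshold is tuned after the results.** The article ties it to the use case and does not say when it is set. AUROC does not depend on it, although sensitivity and specificity do.

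**Conclusion.** The point holds in a limited form. As written, the choice of algorithm rests partly on performance and is not shielded from the results that will be reported, so the internal AUROC of each final model is likely to be overstated.

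For four algorithms within one model type and 100 cases with 200 controls, a null winner averages about 0.52 to 0.54, and its lower limit exceeds 0.5 in about 6% to 21% of studies. The low end comes from the normal approximation at correlation 0.8, the high end from the simulation with refitting. With a true AUROC of 0.70, the overstatement is about 0.015 to 0.034.

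These sizes rest on the assumed number and correlation of candidates, on stand-in learners, and on selection by highest AUROC. The direction of the bias does not depend on them, provided that performance influences the choice. The bias is modest, but it affects the figure that readers will take as the study's main result.

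**What to change.** In Integrative Data Analysis and AI Model Development:

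- State that the algorithm is selected within each outer training set, in the inner loop, by one named metric (for example log loss), and that any data-derived operating threshold is set there too.
- Report the outer-loop performance of this whole procedure once for the preoperative clinical model and once for the integrative model. Alternatively, report the winner only on a temporally separated holdout that played no part in selection.
- Fix the candidate list beforehand, using interpretability to decide what goes on it. Show the individual algorithms side by side, labelled descriptive.
- Allow a result of no usable model.

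Rerunning the procedure on permuted POD labels would be a useful reference but is optional in an exploratory study.

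The cost is wording and computing time, with no new patients or data. The price is a slightly lower reported AUROC and less freedom to pick the algorithm by judgement. The change should be made before outer-loop results have guided any choice.
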